### 6.3 Declaration of interest

The study participants declare no financial and/or other conflicts of interest related to the study.

### 6.4 Dissemination policy:

The Circ. Min. Health N° 6 of 09/02/2002 obliges each researcher who gets any results of interest to public health, to publish the results within 12 months from the end of the study. All the patients will freely agree or disagree to participate to the study in the belief that the results will be useful to improve knowledge about their pathologies, for health benefit from themselves or other patients. To respect their will and in the maximum interest of honest clinical research, the investigators agree on the need to ensure the wide publication and diffusion of their results in a consistent and responsible way under their responsibility. The study coordinator is the official data owner. The steering committee has the right to present methods and results of the study at public symposia and conferences. The principal publications from the trial will be in the name of Investigators with full credit assigned to all collaborating investigators and institutions.

## APPENDIX 2: flow-chart of the study

[figure not shown]

## APPENDIX 3: Sequential Organ Failure Assessment (SOFA) score

| variables                                                                        | 0                                   | 1                                    | 2                                                            | 3                                                                                      | 4                                                                                     |
|----------------------------------------------------------------------------------|-------------------------------------|--------------------------------------|--------------------------------------------------------------|----------------------------------------------------------------------------------------|---------------------------------------------------------------------------------------|
| Central Nervous System
(Glasgow Coma Scale score)                      | 15                                  | 13-14                                | 10-12                                                        | 6-9                                                                                    | <6                                                                                    |
| Respiratory
(PaO 2 / FiO 2 ratio)                | >400                                | ≤ 400                                | ≤ 300                                                        | ≤ 200 A                                                                     | ≤ 200 A                                                                    |
| Cardiovascular, Hypotension
(MAP; mmHg / catecholamine dose; γ/Kg/min) | PAM >70
and NO
catecholamines | PAM < 70
and NO
catecholamines | Dop B ≤ 5
or
Dob B (any
dose) | Dop B >5
or
Epi B ≤ 0,1
or
Norepi B ≤ 0,1 | Dop B > 15 or
Epi B > 0,1
or
Norepi B > 0,1 |
| Coagulation
(Platelets ; x 10  u/μL)                       | >150                                | ≤ 150                                | ≤ 100                                                        | ≤ 50                                                                                   | ≤ 20                                                                                  |
| Liver
(Bilirubin; mg/dl)                                               | <1,1                                | 1,2 - 1,9                            | 2,0 - 5,9                                                    | 6,0 – 11,9                                                                             | >12                                                                                   |
| Renal
(Creatinine; mg/dl
/diuresis ;ml/24h)                         | <1,1
+
diuresis >
500      | 1,2 - 1,9
+
diuresis >
500  | 2,0 - 3,4
+
diuresis >
500                          | 3,5 – 4,9
o
diuresis
<500                                                     | >5
o
diuresis
<200                                                           |

A - Values are with respiratory support.

B – Catecholamines are specified as follow:

|        |                |
|--------|----------------|
| Dop    | Dopamine       |
| Dob    | Dobutamine     |
| Epi    | Epinephrine    |
| Norepi | Norepinephrine |

#### APPENDIX 4: Study timeline

| Time-points                                               |                           | Day-0                                                                                                                                                        | From Day 0 to Say 28 | Day-28 | ICU discharge | Hospital discharge |
|-----------------------------------------------------------|---------------------------|--------------------------------------------------------------------------------------------------------------------------------------------------------------|----------------------|--------|---------------|--------------------|
| Eligibility Screen A                           |                           | X                                                                                                                                                            |                      |        |               |                    |
| Informed consent                                          |                           | X
or as soon as feasible                                                                                                                                  |                      |        |               |                    |
| Allocation                                                |                           | X                                                                                                                                                            |                      |        |               |                    |
| Treatment:                                                | LMWH (group 1)            | 
 
• Enoxaparine from day 0 to ICU discharge
 
                                                                  |                      |        |               |                    |
|                                                           | LMWH + steroids (group 2) | 
 
• Enoxaparine: from day 0 to ICU discharge
 
• Methylprednisolone: from day 0 to day 14
 
             |                      |        |               |                    |
|                                                           | UFH + steroids (group 3)  | 
 
• Unfractionated heparin : from day 0 to ICU discharge
 
• Methylprednisolone: from day 0 to day 14
 
 |                      |        |               |                    |
| Baseline characteristics B                     |                           | X                                                                                                                                                            |                      |        |               |                    |
| Physiological and Processes of care outcomes C |                           |                                                                                                                                                              | X                    | X      |               |                    |
| Safety monitoring                                         |                           |                                                                                                                                                              | X                    |        |               |                    |
| Primary outcome D                              |                           |                                                                                                                                                              |                      | X      |               |                    |
| Secondary outcomes E                           |                           |                                                                                                                                                              |                      | X      | X             | X                  |

A) Eligibility screen:

- Inclusion and exclusion criteria (see 2.2.1 and 2.2.2) including pregnancy test.

B) Baseline characteristics:

- Demographic data (sex, date of birth)
- Medical, Medication and surgical history
- SAPS II score

C) Physiological and Processes of care outcomes:

- Vital signs: mean arterial pressure (MAP), Heart rate (HR), Respiratory rate (RR), diuresis and systemic body temperature and fluid balance will be recorded daily from inclusion to ICU discharge (censored day 28);
- Routine laboratory test parameters for organ function assessment: haemoglobin, platelets count, white blood cells count, troponin, coagulative parameters (INR, PT, aPTT), parameters for liver (AST, ALT, bilirubin) and renal function (creatinine) will be recorded daily from inclusion to day 7 and then at day 14, 21, 28, censored at ICU discharge;
- Blood cells count, C-reactive protein (CRP) and procalcitonin (PCT), IL-6, immunoglobulins titers (IgG, IgA, IgM) will be recorded daily from inclusion to day 7 and then at day 14, 21 and 28, censored at ICU discharge;
- Beta-D Glucan in the blood and/or Galactomannan in the BAL will be recorded at admission and then every 3-5 days, censored at ICU discharge
- Ventilation mode (spontaneous breathing or mechanical ventilation), inspired oxygen fraction and arterial blood gas analysis parameters will be recorded daily from inclusion to ICU discharge, censored at day 28;
  - Adjunctive treatment such as pronation cycles, Nitric Oxide or ECMO will be recorded daily from inclusion to ICU discharge from (censored at day 28);
- New blood, respiratory and urinary-tract infections and the implicated microorganisms will be recorded from randomization to day 28;
- Viral reactivation measured by ADENOVIRUS, HSV e CMV DNA titres will be recorded from randomization to day 28, censored at ICU discharge;
- Need of renal replacement therapy: from randomization to 28 days, censored at ICU discharge.

D) Primary Outcome:

- All-cause mortality will be measured at day 28.

E) Secondary Outcomes:

- All-cause mortality will be measured at ICU discharge and hospital discharge
- SOFA score and its components will be recorded daily from randomization to ICU discharge (censored at day 28);
- Ventilation free days (VFDs) at day 28, measured at day 28;
- ICU free days (IFDs) at day 28, measured at day 28;
- Need of rescue administration of high-dose steroids or immune-modulatory drugs, measured from randomization to ICU discharge, censored at day 28;
- Switch from non-invasive to invasive mechanical ventilation from randomization to ICU discharge, censored at day 28;
- Occurrence of new infections will be recorded from randomization to day 28;
- Occurrence of objectively confirmed venous thromboembolism, stroke or myocardial infarction will be recorded from randomization to day 28;
- Occurrence of protocol related adverse events (see chapter 5.2) at day 28 (safety endpoint).

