### **2.4.2 Secondary Endpoints:**

- Ventilation free days (VFDs) at day 28, defined as the total number of days that patient is alive and free of ventilation between randomisation and day 28 (censored at hospital discharge). Ventilation is considered as positive pressure ventilation, either invasive or non-invasive. Periods of assisted breathing lasting less than 24 hours for surgical procedures will not count against the ventilation free days calculation;
- Need of rescue administration of high-dose steroids or immune-modulatory drugs;
- Occurrence of switch from non-invasive to invasive mechanical ventilation during ICU-stay;
- Delay from start of non-invasive ventilation to switch to invasive ventilation;
- All-cause mortality at ICU discharge and hospital discharge;
- ICU free days (IFDs) at day 28, defined as the total number of days between ICU discharge and day 28. If death occurs during the ICU stay before day 28 the ICU free days calculation will be 0. The ICU readmission before day 28 after randomization will be considered;
- Occurrence of new infections from randomization to day 28; including infections by Candida, Aspergillus, Adenovirus, Herpes Virus e Citomegalovirus
- Occurrence of new organ dysfunction and grade of dysfunction during ICU stay. Organ dysfunction is defined as a Sequential Organ Failure Assessment (SOFA) score  $\geq 3$  occurring after randomization, grade of dysfunction is measured with SOFA score (see SOFA score in APPENDIX 4) daily from randomization to ICU discharge (censored at day 28);
- Objectively confirmed venous thromboembolism, stroke or myocardial infarction;
- Occurrence of major bleeding (safety end point), defined as transfusion of 2 or more units of packed red blood cells in a day, bleeding that occurs in at least one of the following critical sites [intracranial, intraspinal, intraocular (within the corpus of the eye; thus, a conjunctival bleed is not an intraocular bleed), pericardial, intra-articular, intramuscular with compartment syndrome, or retroperitoneal], bleeding that necessitates surgical intervention and bleeding that is fatal (defined as a bleeding event that was the primary cause of death or contributed directly to death);

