### **2.4.3 Physiological and Processes of care outcomes**

- Vital signs such as mean arterial pressure (MAP), heart rate (HR), respiratory rate (RR), diuresis and systemic body temperature and fluid balance will be recorded daily from inclusion until ICU discharge (censored day 28);
- Routine laboratory test parameters for organ function assessment: haemoglobin, platelets count, white blood cells count, troponin, coagulative parameters (INR, PT, aPTT), parameters for liver (AST, ALT, bilirubin) and renal function (creatinine) will be recorded daily from inclusion to ICU discharge (censored at day 28);
- Blood cells count, C-reactive protein (CRP), procalcitonin (PCT) and interleukin 6 (IL-6) will be recorded daily from inclusion to ICU discharge (censored at day 28);
- Ventilation mode, inspired oxygen fraction and arterial blood gas analysis parameters will be recorded daily from inclusion to ICU discharge from (censored at day 28);
- Adjunctive treatment such as pronation cycles, Nitric Oxide or ECMO will be recorded daily from inclusion to ICU discharge from (censored at day 28);
- New blood, respiratory and urinary-tract infections will be recorded from randomization to day 28;
- Viral reactivation measured by CMV DNA titres will be recorded from randomization to day 28;
- Need of new renal replacement therapy (intermittent haemodialysis or continuous veno-venous hemofiltration) from randomization to 28 days.

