SAPS II) will be calculated by the data from the first 24 h of ICU stay. During the study duration clinical and laboratory parameters will be evaluated and recorded following the timeline schedule in APPENDIX 4: SOFA score and its components, vital signs such as mean arterial pressure (MAP), heart rate (HR), respiratory rate (RR), systemic temperature, diuresis, fluid balance, data from routine laboratory test such as haemoglobin, platelets count, white blood cells count, troponin, coagulative parameters (INR, PT, aPTT), parameters for liver and renal function (AST, ALT, bilirubin, creatinine), oxygen inspired fraction, blood gas analysis results (BGA), ventilation mode, need of adjunctive therapy for ARDS (i.e. prone position, Nitric oxide, ECMO), blood cells count, C-reactive protein (PCR), procalcitonin (PCT), interleukin-6 (IL-6), immunoglobulin titers (IgG, IgM, IgA), occurrence of ICU-acquired (from 48 hours after ICU admission) blood, respiratory and urinary-tract infection and the implicated microorganisms, reactivation of viral infections (CMV-DNA titres). Other recorded parameters will include duration and mode of ventilatory support in days, duration and type of antiviral, antibiotic and antifungal therapy in days, need of vasoactive drugs, use of immune-modulatory drugs or other adjunctive treatment for COVID-19 pneumonia.

As a blood-bank for possible further biochemical investigations (e.g. cytokines titers, different biomarkers), for each patient who will be included in the study a blood sample of about 6 ml will be collected at baseline, day 7 and 28 or at ICU discharge and stored, after centrifugation, at -70°C in the local laboratory of each site.

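### Ventilation-free days run to day 28 or hospital discharge, but the scheduled daily ventilation record ends at ICU discharge

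*Protocol*

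**What the plan says.** **Endpoint.** Protocol section 2.4.2 lists VFDs first among the secondary endpoints. It counts the days on which the patient is "alive and free of ventilation between randomisation and day 28 (censored at hospital discharge"). It then says what counts: "Ventilation is considered as positive pressure ventilation, either invasive or non-invasive".

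**Daily record.** Section 2.4.3 states: "Ventilation mode, inspired oxygen fraction and arterial blood gas analysis parameters will be recorded daily from inclusion to ICU discharge", with day 28 as the latest limit. Appendix 4, list C, repeats this and adds two categories in brackets: "Ventilation mode (spontaneous breathing or mechanical ventilation), inspired oxygen fraction and arterial blood gas analysis parameters will be recorded daily from inclusion to ICU discharge".

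**Other places that bear on it.**
- Section 4.1 sends the daily clinical parameters, ventilation mode among them, to the Appendix 4 schedule. It then adds a separate item: "Other recorded parameters will include duration and mode of ventilatory support in days". No start or end is given for that item.
- Appendix 4, list E, gives the time-point of the endpoint: "Ventilation free days (VFDs) at day 28, measured at day 28".
- On returns to intensive care, section 2.4.2 says: "The ICU readmission before day 28 after randomization will be considered". That sentence belongs to the definition of ICU-free days. The VFD definition does not mention readmission.

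**The concern.** The endpoint stops at hospital discharge or day 28, while the daily data stop at ICU discharge. Ward days between the two belong to the endpoint but not to the daily record. A site that follows the schedule exactly would hold no daily ventilation status for a patient stepped down on non-invasive support. The same applies to a patient readmitted and ventilated again, unless the site resumed recording of its own accord.

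An analysis plan cannot repair this later. It can set a rule for days without data, but it cannot supply ward data that the schedule never asked for. The trial is open-label, so step-down practice could in principle differ between arms. Incomplete recording would then fall unevenly on the comparison.

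**Working it through.** The protocol states no expected mean, standard deviation, ward-ventilation rate or readmission rate for VFDs, so there is no figure to reproduce. The planned 210 patients are sized on 28-day mortality and do not enter this check.

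**Step 1: set the windows side by side.**

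| Place | Item | Ends at |
|---|---|---|
| 2.4.2 | VFD definition | Day 28, censored at hospital discharge |
| 2.4.3 | Daily ventilation mode | ICU discharge, at most day 28 |
| Appendix 4, list C | Daily ventilation mode, two categories | ICU discharge, at most day 28 |
| 4.1 | Daily parameters | As Appendix 4 |
| 4.1 | Duration and mode of support | Not stated |
| Appendix 4, list E | VFDs | Time-point day 28; no data source named |

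The ICU limit does not look like a slip. In Appendix 4, new infections and thrombotic events run from randomisation to day 28 with no ICU stop, whereas ventilation mode carries one.

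**Step 2: length of the gap.** Let D be the day of ICU discharge and H the day of hospital discharge. The days inside the endpoint window but outside the daily record number min(28, H) − D.

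**Step 3: one patient (all values assumed).** The patient is ventilated throughout the ICU stay, leaves the ICU on day 12, has non-invasive ventilation on the ward to day 18, and is alive in hospital on day 28.
- By the section 2.4.2 definition: 28 − 18 = 10 VFDs.
- By the daily record: 28 − 12 = 16 days have no ventilation status. If they are left missing, the count could lie anywhere from 0 to 16. If they are scored as free, it is 16, which is 16 − 10 = 6 too many.

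**Step 4: an arm mean (assumed values).** If a share q of the arm has w unrecorded ventilated days each, and these are scored as free, the mean is overstated by q × w.

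| q | w = 2 | w = 5 |
|---|---|---|
| 5% | 0.10 | 0.25 |
| 10% | 0.20 | 0.50 |
| 20% | 0.40 | 1.00 |

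With q = 15% and the 6 days of Step 3, the result is 0.15 × 6 = 0.9 day. With q = 0 it is zero. Section 4.2.1 compares continuous outcomes by the difference of means. That difference is distorted only by the gap between two arms' values of q × w; equal values cancel.

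**Step 5: the categories.** VFDs need one answer per day: positive pressure ventilation or none. Two categories can give it, provided that non-invasive ventilation is assigned to one of them. The bracket in Appendix 4 does not assign it. A patient on non-invasive support is breathing spontaneously, so sites could code the same day differently.

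**The case against.** The best defence is that the daily item need not be the source of VFDs. Appendix 4 places ventilation mode in list C, beside blood gases, and VFDs in list E. Within list E, rescue treatment and the switch to invasive ventilation are limited to the ICU stay, but VFDs are not. Section 4.1 collects duration and mode of support separately, without an ICU limit, and draws on the clinical documentation. Later ventilation could therefore be captured.

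This stands as far as it goes, and it rules out several stronger readings that a reader might draw:

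- **That VFDs cannot be computed at all.** The documents do not show this, because the section 4.1 item might be filled in for the whole hospital stay.
- **That ward ventilation will be scored as ventilation-free, so that the error runs one way.** No scoring rule is stated; such days could equally be missing.
- **That two categories are too few.** They suffice once non-invasive ventilation is assigned. Section 2.4.3 and section 4.1 speak of mode without the bracket, and the switch from non-invasive to invasive ventilation is itself recorded.
- **That the protocol promises to handle readmission in VFDs.** The sentence concerns ICU-free days. It shows only that readmissions are expected.

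The defence does not close the gap. An item with no window does not tell sites to go on recording after ICU discharge, and a day-28 time-point is not a source of ward data. The only ventilation instruction with an explicit window stops at ICU discharge.

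**Conclusion.** The mismatch between the endpoint window and the daily recording window is real and rests on the text alone. For patients with positive pressure ventilation on the ward or after ICU readmission, VFDs cannot be derived from the scheduled daily record. The days are then missing or, under a rule that the protocol does not state, VFDs are overstated.

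The size cannot be computed from the document. The range of 0.1 to 1.0 day per arm mean is an illustration. It rests on assumed shares and durations and on scoring unrecorded days as free. A difference in step-down practice between arms is a possibility that the open-label design leaves open; nothing in the protocol shows that it will occur.

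This should be corrected, but it concerns one secondary endpoint. The primary endpoint of 28-day mortality and the sample size are not affected.

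**What to change.** Reconcile sections 2.4.2, 2.4.3, 4.1 and Appendix 4 on four points:

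1. **Window.** Record ventilation status from randomisation to day 28 or hospital discharge, whichever is first, including ward days and any ICU readmission, in all three arms.
2. **Coding.** Record positive pressure ventilation as yes or no, and state that non-invasive ventilation counts as yes. Replace or define the bracket in Appendix 4 accordingly.
3. **Section 4.1.** Give the item on duration and mode of support the same window, and say whether it or the daily record is the source for VFDs.
4. **Readmission.** State in the VFD definition that ventilation during an ICU readmission counts.

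Daily entry on the ward is not essential. Start and stop dates of each ventilation episode, collected at the existing day-28 assessment, would suffice.

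The cost is slightly more data entry after ICU discharge and a small change to the eCRF.
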